### Anesthesia management

All patients are given Tracheal Intubation General Anesthesia. Premedication is not permitted in either group, including anticholinergic drugs or sedatives. After entering the operating room, venous access is established, if necessary, radial artery catheterization is performed. Then, multi-functional monitor is connected. Non-invasive blood pressure (or invasive arterial blood pressure), blood oxygen saturation, electrocardiography, PETCO2, and depth of anesthesia are measured. Anesthesia is induced with propofol (1.5–2.5 mg/kg) and sufentanil (0.3-0.5ug/kg). A low dose of Rocuronium (0.8 mg/kg) is administered to facilitate intubation. After tracheal intubation, mechanical ventilation with 60% oxygen in air is applied and adjusted to achieve the end-tidal carbon dioxide partial pressure between 35 to 45 mmHg. Anesthesia is maintained with end-tidal concentration of sevoflurane (1%-2.5%), plus a continuous infusion of refentanil (5–10 ug · kg − 1 · *h* − 1), and cisatracurium 0.3 mg/kg per hour. During the operation, the infusion rates of propofol and refentanil are adjusted to maintain hemodynamic stability. All participants in both groups will receive standardized multimodal antiemetic prophylaxis consisting of 5 mg dexamethasone (administered at anaesthesia induction) and 8 mg ondansetron (administered before the end of surgery). Supplemental postoperative analgesia is provided at the discretion of attending anesthesiologist or patient and could include opioids, nonsteroidal anti-inflammatory drugs, and other analgesics.

### Study intervention

Before anesthesia, an anesthesia assistant not involved in data collection will open the opaque envelopes containing randomized sequences and then adjust the parameters of the taVNS device. In both groups, the electrodes will be placed on the concha of the left ear and electrical stimulation will be delivered identically (pulse width, 200 microseconds; frequency, 20 Hz). The current intensity will be increased for 30 s until the participant reports a tingling sensation. Then the intensity will be decreased to a comfort level slightly below the above threshold. Following induction of anesthesia, the taVNS group patients will receive electrical stimulation lasting for 30 min according to the predefined parameters. In sham group, patients will not receive electrical stimulation by keeping device remain off for 30 min to maintain the sham state. Based on the anatomical evidence that the right ABVN innervates the sinoatrial node and may exert adverse effects on heart rate, electrical stimulation will be delivered *via* electrodes on the left concha of the ear in all participants [21]. During the intervention period, patients will be closely monitored for ECG, blood pressure, and pulse oxygen saturation (SpO_2_). Once severe bradycardia, high-degree AV block, or significant hypotension occurs, the stimulation will be immediately terminated and the following conditions will be considered as dropout cases, and the reason and date of dropout will be recorded in a case report form.

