### Statistical plan

Two members of the research team will perform study consolidation and analysis. All statistical plans will be finalized prior to unblinding. Categorical data will be expressed as frequencies and percentages and continuous variables will be expressed as means and standard deviations for normally distributed variables or otherwise as medians and interquartile range. The Kolmogorov–Smirnov test will be used to detect the normality of distribution. The statistical analysis will be conducted using R software (version 4.3.1 or higher) and SAS software (version 9.4 or higher).

Patient demographic and baseline characteristics will be summarized using descriptive statistics for each group. No hypothesis testing will be performed for between-group comparisons at baseline. The balance between the taVNS and the sham group will be evaluated by calculating standardized mean differences (SMDs), with an SMD > 0.10 indicating substantial imbalance.

The primary endpoint, the incidence of PONV within 24 h postoperatively, will be analyzed in both the intention-to-treat (ITT) population (all randomized patients) and the per-protocol (PP) population (excluding patients with major protocol deviations, such as failure to apply stimulation, incorrect stimulation parameters, or surgical conversion). Between-group comparisons for the primary endpoint will be performed using the Chi-square test or Fisher’s exact test, as appropriate. The treatment effect will be reported as relative risk (RR) with a 95% confidence interval (CI). A multivariable logistic regression model will be fitted to adjust for potential confounding factors (baseline covariates with SMD > 0.10), with results presented as an adjusted odds ratio (OR) with 95% CI. Missing data for the primary endpoint will be handled under the missing-at-random assumption using multiple imputation.

All secondary endpoints will be analyzed in the ITT population only. The severity of postoperative nausea (NRS scores) will be compared between groups using the independent t-test or Mann-Whitney U test, with the effect size reported as the difference in means or medians with 95% CI. The use of rescue antiemetics and patient satisfaction scores will be compared using the Chi-square test (or Fisher’s exact test) and the Mann-Whitney U test, respectively. A Bonferroni correction will be applied for the three secondary endpoint comparisons, setting the significance level at *p* < 0.017 (0.05/3).

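### Patients whose stimulation is stopped for a haemodynamic event are labelled dropouts, and this is not reconciled with the all-randomized ITT set or the 24 h PONV follow-up

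*Protocol article*

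**What the plan says.** Four parts of the Protocol article bear on this.

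- **Study intervention.** The trigger reads "Once severe bradycardia, high-degree AV block, or significant hypotension occurs". The consequence is that "the stimulation will be immediately terminated and the following conditions will be considered as dropout cases". No list of conditions follows, so the label can attach only to the events just named. On documentation, the article adds only that "the reason and date of dropout will be recorded in a case report form". For the other arm: "In sham group, patients will not receive electrical stimulation by keeping device remain off for 30 min".
- **Outcome and Table 1.** Nausea and vomiting are actively asked about at 1, 2, 6, 12 and 24 h. No exception is made for a patient whose stimulation was cut short.
- **Statistical plan.** The primary endpoint is analysed in "the intention-to-treat (ITT) population (all randomized patients") and also per protocol. For gaps, "Missing data for the primary endpoint will be handled under the missing-at-random assumption using multiple imputation".
- **Data collection.** Hypotension and bradycardia episodes and all adverse events are recorded for every patient.

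The article does not say whether follow-up continues after a patient becomes a dropout case.

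**The concern.** Stopping a 30-minute intraoperative stimulation and leaving the trial are different events. A patient whose stimulation was stopped can still be asked about nausea and vomiting over the next 24 h. Under an all-randomized ITT analysis, that observed answer is what should be analysed.

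The dropout label, with its date, invites site staff to end follow-up. If they do, an observable primary outcome becomes a missing one and is filled in under missing at random. The reason for the loss would be a haemodynamic event that vagal stimulation might cause; the article itself chooses the left ear because of possible heart-rate effects on the right. If such patients also differ in PONV risk, and if the loss falls more on the taVNS arm, the estimated effect is biased. If follow-up does continue, dropout is the wrong word. In either case the sections need to be reconciled.

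**Working it through.** **Step 1. The plan's own figure.** Sample size gives 40% vs 20%, alpha 0.05, power 0.80 and 158 patients. With a two-sided test and unpooled variance:

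n = (1.960 + 0.842)² × (0.4×0.6 + 0.2×0.8) / 0.2² = 78.49, so 79 per arm and 158 in total.

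The figure reproduces. The target of 200 allows for a loss of 1 − 158/200 = 21%. The stated reasons are protocol deviations and withdrawal of consent; safety stops are not named.

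**Step 2. Bias when there is no true effect.** The article gives no rate of stopped stimulation and no PONV rate among stopped patients, so both are assumed. Let k of 100 taVNS patients lose their outcome, with PONV risk r. Take no loss in sham, and 40% PONV in both arms.

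Remaining taVNS rate = (40 − k×r) / (100 − k); apparent RR = that rate / 0.40.

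| k | r | remaining taVNS rate | apparent RR |
|---|---|---|---|
| 2 | 0.6 | 38.8/98 = 39.6% | 0.99 |
| 2 | 0.8 | 38.4/98 = 39.2% | 0.98 |
| 5 | 0.6 | 37/95 = 38.9% | 0.97 |
| 5 | 0.8 | 36/95 = 37.9% | 0.95 |
| 10 | 0.6 | 34/90 = 37.8% | 0.94 |
| 10 | 0.8 | 32/90 = 35.6% | 0.89 |

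With r = 0.4 the RR is 1.00 for any k. With r below 0.4 the bias runs against taVNS: k = 10 and r = 0.2 gives 38/90 = 42.2%, RR 1.06.

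**Step 3. Loss in both arms, no true effect.**

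- 10 lost in taVNS and 2 in sham, r = 0.6: 37.8% vs 38.8/98 = 39.6%, RR 0.95. The two-sided type I error on completers is about 0.058.
- The same with r = 0.8: 35.6% vs 38.4/98 = 39.2%, RR 0.91, type I error about 0.081.
- 10 lost in each arm at the same risk: RR 1.00, type I error 0.05.

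**Step 4. Under the planned effect (40% vs 20%).** With 5 lost in taVNS and 1 in sham, r = 0.6 in both: (20 − 3)/95 = 17.9% vs (40 − 0.6)/99 = 39.8%. The RR is 0.45 instead of 0.50. With 10 and 2 lost: 14/90 = 15.6% vs 39.6%, RR 0.39.

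**Step 5. How this relates to the planned imputation.** Steps 2 to 4 are computed on completers, whereas the plan imputes. Imputation within arm that does not use the trigger event gives back roughly the completers' rate, so the RRs carry over approximately. A model that uses the recorded episodes could do better. However, if every patient with a qualifying event lost the outcome, no such patient would have an observed outcome to inform the model.

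**Step 6. Power.** With 100 per arm retained, power for 40% vs 20% is 87.6% (pooled) or 88.5% (unpooled). If only numbers are lost, pooled power is 86.5% with 5 and 1 lost, and 85.3% with 10 and 2 lost. The issue is bias, not power.

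**The case against.** The strongest reply is that the text does less than the word dropout suggests, and several stronger readings are not supported.

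- **A reader might infer a flat contradiction with ITT.** The article never removes these patients from the all-randomized set. A dropout can remain in it, observed or imputed. The fault is that the sections are unreconciled.
- **A reader might infer that outcomes will certainly be lost.** That is only the ordinary meaning of dropout. The assessment schedule has no exception, and the sentence points to a list that does not appear and may stand in the full protocol.
- **A reader might infer removal strictly by arm.** The trigger is worded for patients generally, and hypotension or bradycardia can occur under the common anaesthetic regimen. Randomization and blinding describes a blinded care team and a device hidden in an opaque bag, so the rule could be invoked in either arm. Unequal loss is plausible because only taVNS has a current to stop, but it is not established.
- **A reader might infer that the safety record loses these patients.** It does not. Data collection records the episodes and all adverse events, and the Statistical plan summarises adverse events by group.
- **A reader might infer an arm-specific per-protocol set** from the examples "such as failure to apply stimulation, incorrect stimulation parameters, or surgical conversion". That list is illustrative, and surgical conversion applies to both arms.

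The Discussion also reports no bradycardia or hypotension observed with left-ear stimulation, which points to the low end of the range. All of this limits the size of the problem. What remains is that the article states a dropout rule for patients whose primary outcome can still be observed, and nothing tells staff to keep collecting it.

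**Conclusion.** The point holds as a failure to reconcile the dropout label with the all-randomized ITT set and the 24 h inquiry. Followed in its ordinary sense, the label would discard observable primary outcomes and replace them with imputation after an event that may be treatment-related.

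The size depends on three assumptions that the article cannot settle: how many are lost, how unequally, and at what PONV risk. With no true effect, no sham loss, 60–80% PONV among those lost, and imputation that only reproduces the completers' rate, the apparent RR is 0.99–0.98 for 2 lost and between 0.97 and 0.89 for 5–10 lost. It is 1.00 if loss and risk are equal in the two arms, or if stopped patients have the same risk as the rest. The effect is probably small if the events are rare. It is still worth correcting now, because recruitment is under way (Study population) and a 24 h outcome that was not collected cannot be recovered.

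**What to change.** 1. In Study intervention, replace the dropout wording with premature discontinuation of study stimulation, and state that this is not withdrawal from the trial. Supply the missing list of conditions or delete the reference to it. On the case report form, record the reason and time of discontinuation separately from any withdrawal.
2. State that all assessments from 1 to 24 h are completed after such a discontinuation.
3. In the Statistical plan, state that these patients are analysed in their assigned arm in the ITT analysis with the outcome observed.
4. Reserve multiple imputation for outcomes that are truly unobserved, for example after withdrawal of consent.

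The clinical criteria for stopping stimulation are not part of this point. The cost is wording in the protocol and analysis plan, a case report form field, and a note to site staff. The assessments are already scheduled for every patient, and the sample size does not change.

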### Outcome

The primary endpoint is the incidence of postoperative nausea and vomiting (PONV) within the first 24 h after surgery. PONV is defined as the occurrence of any episode of nausea (an unpleasant subjective sensation associated with the urge to vomit) and/or vomiting (the forceful expulsion of gastric contents) during this period. The incidence will be assessed by active inquiry and documentation of the occurrence of these symptoms at 1, 2, 6, 12, and 24 h postoperatively. The primary outcome measure will be the proportion of patients experiencing at least one episode of nausea or vomiting within the first 24 h postoperatively.

Secondary endpoints are as follows: the severity of nausea or/and vomiting at 1, 2, 6, 12, and 24 h postoperatively, assessed using a 0–10 numerical rating scale (NRS), which is a patient self-assessment tool involves drawing a 10 cm line on paper, with 0 indicating no symptoms of nausea and 10 indicating excruciating severe vomiting; the types and dosage of drugs used for rescue antiemetic therapy within 24 h after surgery; and a 5-point Likert satisfaction scale with taVNS for the management of nausea and vomiting, with 1 to 5 points indicating ‘strongly disagree’ to ‘strongly agree’ respectively (supplemental file S2). In addition, consumption of opioids within 24 h after surgery converted to intravenous morphine milligram equivalents (MME); the autonomic nervous function assessed *via* heart rate variability (HRV) parameters (low-frequency/high-frequency ratio) at baseline (pre-induction), at the end of surgery, and at 24 h postoperatively, as well as the treatment effect of taVNS on the primary endpoint (PONV incidence) across predefined patient subgroups based on age strata and Apfel score categories are further explored.

### Data collection

Data will be collected using dedicated case report forms (CRFs) and managed in a secure electronic database. The demographic and baseline data include age, height, weight, BMI, ASA physical status, Apfel risk score, smoking status, history of motion sickness/PONV, comorbidities, and preoperative medications. Intraoperative data include anesthetic doses (propofol, remifentanil, volatile agents), vital signs at key time points, episodes of hypotension/bradycardia with interventions, surgical duration, fluid administration, and taVNS/Sham protocol details (group assignment, stimulation parameters, duration). Postoperative data include incidence of PONV assessed at 1 h after PACU arrival and 2, 6, 12, and 24 h postoperatively, nausea severity (11-point NRS) at the above time points, use and dose of rescue antiemetics within 24 h, and patient satisfaction (5-point Likert scale) at 24 h. Additional data collected include all adverse events (e.g. skin erythema, dizziness) with details on their nature, severity, and relationship to the intervention; heart rate variability; 24-hour postoperative opioid consumption; the total cumulative consumption of opioid analgesics; and blinding assessment (patient guess).

### Sample size

The sample size was calculated with the PASS 15.0 software. It is reported the incidence of PONV among Chinese patients undergoing elective gynecological laparoscopic surgery is approximately 40% following dual-agent prophylaxis with dexamethasone and ondansetron [5]. Based on previous studies, we assume that the incidence of PONV in the taVNS group would be reduced to 20%[22,23]. To provide a significance level of 0.05 and a power of 0.8, a sample size of 158 patients will be required. Considering potential protocol deviations and withdrawal of consent, the recruitment target will be increased to 100 patients in each group.

### Statistical plan

Two members of the research team will perform study consolidation and analysis. All statistical plans will be finalized prior to unblinding. Categorical data will be expressed as frequencies and percentages and continuous variables will be expressed as means and standard deviations for normally distributed variables or otherwise as medians and interquartile range. The Kolmogorov–Smirnov test will be used to detect the normality of distribution. The statistical analysis will be conducted using R software (version 4.3.1 or higher) and SAS software (version 9.4 or higher).

Patient demographic and baseline characteristics will be summarized using descriptive statistics for each group. No hypothesis testing will be performed for between-group comparisons at baseline. The balance between the taVNS and the sham group will be evaluated by calculating standardized mean differences (SMDs), with an SMD > 0.10 indicating substantial imbalance.

The primary endpoint, the incidence of PONV within 24 h postoperatively, will be analyzed in both the intention-to-treat (ITT) population (all randomized patients) and the per-protocol (PP) population (excluding patients with major protocol deviations, such as failure to apply stimulation, incorrect stimulation parameters, or surgical conversion). Between-group comparisons for the primary endpoint will be performed using the Chi-square test or Fisher’s exact test, as appropriate. The treatment effect will be reported as relative risk (RR) with a 95% confidence interval (CI). A multivariable logistic regression model will be fitted to adjust for potential confounding factors (baseline covariates with SMD > 0.10), with results presented as an adjusted odds ratio (OR) with 95% CI. Missing data for the primary endpoint will be handled under the missing-at-random assumption using multiple imputation.

All secondary endpoints will be analyzed in the ITT population only. The severity of postoperative nausea (NRS scores) will be compared between groups using the independent t-test or Mann-Whitney U test, with the effect size reported as the difference in means or medians with 95% CI. The use of rescue antiemetics and patient satisfaction scores will be compared using the Chi-square test (or Fisher’s exact test) and the Mann-Whitney U test, respectively. A Bonferroni correction will be applied for the three secondary endpoint comparisons, setting the significance level at *p* < 0.017 (0.05/3).

Exploratory analyses (e.g. heart rate variability parameters, postoperative opioid consumption) will be conducted in the ITT population without correcting for multiple comparisons. Effect estimates with 95% CIs will be reported for these endpoints, but P-values will not be emphasized. Subgroup analyses of the primary endpoint will be performed based on predefined factors such as age strata and Apfel score categories. Interaction terms will be tested in regression models to assess effect modification.

Safety data, including the incidence of adverse events, will be summarized descriptively by treatment group.

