### Randomization and blinding

After informed consent is obtained, block randomization is employed. An independent administrator not involved in this study sets a block length of 4, generating a random sequence using the online Sealed Envelope tool. Participants are randomized in a 1:1 ratio to either the taVNS group or the sham group. During this process, allocation concealment is guaranteed by using sealed envelopes and the anesthesiologist responsible for the surgery has no a priori knowledge of the intervention assignment. The medical team providing care during the perioperative period, outcome assessors, investigators, and patients are also blinded to the group assignment. After the participant enters the operating room, an anesthesia assistant who is not involved in the data collection and outcome assessment opens the envelope in the absence of the anesthesiologist, assigns the patient to either the taVNS or the sham group, sets the vagus nerve electrical stimulation parameters, and places the vagus nerve electrical stimulation device into an opaque black bag. The anesthesiologist then performs anesthesia induction immediately. Due to the anterograde amnesic effect of anesthesia, the patient remains unaware of the intervention postoperatively. To ensure the effectiveness of patient blinding, a random selection of patients is surveyed before unblinding to determine which group they believed they had been assigned to. The proportion is then calculated, and if it is close to 1:1, it indicates successful blinding. Follow-up personnel and ward staff remain unaware of the group assignments. After statistical results are generated, unblinding is performed for all participants.

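### The supportive adjusted model of the primary endpoint picks its covariates by an SMD threshold that chance alone exceeds about half the time, so known PONV predictors enter or drop out almost at random

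*Protocol article*

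**What the plan says.** The Statistical plan compares the primary endpoint between groups by an unadjusted chi-square or Fisher's exact test and reports a relative risk (RR) with 95% CI. It then adds a second analysis of the same endpoint, a multivariable logistic model "fitted to adjust for potential confounding factors (baseline covariates with SMD" above 0.10), reported as an adjusted odds ratio (OR). The same section rules out hypothesis tests at baseline and describes balance by SMDs instead, "with an SMD > 0.10 indicating substantial imbalance". No covariate is guaranteed a place in the model.

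The candidates are in the Data collection section: "The demographic and baseline data include age, height, weight, BMI, ASA physical status, Apfel risk score, smoking status", followed by history of motion sickness or PONV, comorbidities and preoperative medications, about 10 items in all. The Introduction names non-smoking and a history of PONV among the independent risk factors. The planned subgroup analyses use age and Apfel score.

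On size and allocation, "the recruitment target will be increased to 100 patients in each group", and "Participants are randomized in a 1:1 ratio to either the taVNS group or the sham group". The independent administrator "sets a block length of 4, generating a random sequence using the online Sealed Envelope tool"; no stratification factor is described.

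**The concern.** In a randomized trial, adjusting for a covariate is useful because it predicts the outcome, whether or not it happens to be balanced. The plan selects on observed imbalance instead. If the threshold lies well inside the range that chance produces at this sample size, entry to the model is close to a coin toss. A strong predictor is dropped when it happens to be balanced, and overlapping items such as height, weight and BMI can enter together.

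At stake is the adjusted OR. A conditional OR is defined by the covariates it conditions on, so a covariate set fixed by chance gives an estimate whose meaning is not known in advance. Part of the gain in precision is also given up.

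**Working it through.** **1. The plan's own sample size.** Inputs from the Sample size section: 40% versus 20%, alpha 0.05 (two-sided assumed), power 0.80. With unpooled variance, n = (0.24 + 0.16) × (1.960 + 0.842)² / 0.20² = 78.5, so 79 per arm and 158 in total. This matches the stated figure. The trial is therefore sized on an unadjusted comparison, and the point below does not touch it.

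**2. How often chance alone gives an SMD beyond 0.10.** Under randomization without stratification, the SMD of a covariate is approximately N(0, 2/n) with n per arm, so P(|SMD| > 0.10) = 2[1 − Φ(0.10/√(2/n))].

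| n per arm | SE = √(2/n) | 0.10/SE | Probability |
|---|---|---|---|
| 100 | 0.141 | 0.71 | 48.0% |
| 90 | 0.149 | 0.67 | 50.2% |
| 79 | 0.159 | 0.63 | 53.0% |

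Simulation agrees. At 100 per arm it gives 48.3% for a continuous covariate and 48.6% to 52.6% for binary covariates with prevalence between 5% and 90%. At 79 per arm it gives 53.3%, and 51.9% to 57.9%. Blocks of 4 keep the arms equal in size but do not constrain covariates. Read literally as a signed SMD, the rule would be met 24.0% of the time at 100 per arm; the absolute value is the usual reading.

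**3. How many enter.** Expected number = 10 × 0.48 = 4.8. An expected count does not need independence. The probability that none enters does, so it is not used here: height, weight and BMI are related, and so are Apfel score, smoking and PONV history.

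**4. How often a predictor is left out.** For any one factor, 1 − 0.48 = 52%. For three factors, if independent, at least one is left out with probability 1 − 0.48³ = 89%, and all three with probability 0.52³ = 14%.

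**5. Consequence, by illustrative simulation.** The documents give no prognostic effect sizes, so these are assumptions.

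- *Scenario A:* 100 per arm; 10 independent covariates, three of them prognostic (log-OR 0.7, 0.5 and 0.5 per SD); conditional treatment OR 0.375; 6,000 runs.
- *Scenario B:* 40% versus about 20%; two prognostic covariates (log-OR 1.0 and 0.5 per SD) and nine noise covariates; 1,500 runs.

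| | Unadjusted | SMD-selected | Prespecified prognostic set |
|---|---|---|---|
| Power, A | 76.0% | 79.3% | 82.9% |
| Power, B | 85.4% | 87.7% | 91.5% |
| Type I error, A | 5.1% | 4.0% | 4.9% |
| Mean log-OR, A | −0.839 | −0.935 | −1.018 |

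The SMD rule costs 82.9 − 79.3 = 3.6 points in A and 91.5 − 87.7 = 3.8 points in B against the prespecified set. It keeps 3.3 of the 6.9 points that adjustment gains in A, and 2.3 of 6.1 in B. The last row shows the shift in meaning: exponentiated, the mean estimates are 0.43, 0.39 and 0.36 for one and the same treatment effect. The selected model lies between the other two because its covariates vary from run to run.

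**The case against.** The strongest reply is that this model is not the primary analysis. That stands: no primary p-value, RR or sample-size figure depends on the SMD rule. A reader might infer from a data-driven model that the trial's main result rests on chance imbalances, but the Statistical plan does not support that.

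A reader might also infer that selection inflates false positives. It uses baseline data and not outcomes, and in Scenario A its type I error is 4.0%, slightly conservative.

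A third tempting reading is a conflict with the sentence "All statistical plans will be finalized prior to unblinding". There is none. The rule itself is fixed in advance, SMDs can be computed on masked group codes, and the Randomization and blinding section places unblinding after the statistical results are generated. What is unknown beforehand is only which covariates the rule will pick.

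It is fair, too, that the predictors may be weaker here than the simulations assume. The participants are women, and the Study population section describes those enrolled as having no history of motion sickness and no plan for opioids within 24 h. Smoking and prior PONV are the main named factors left to vary at baseline. The power loss is also measured against a model that the plan does not propose; in both scenarios the SMD-selected model still has more power than the unadjusted test.

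The change from RR to OR is a separate and lesser matter. At 40% versus 20% the RR is 0.50 and the OR is (0.2/0.8)/(0.4/0.6) = 0.375, so the second figure looks more extreme for the same effect. The plan labels it correctly as an OR.

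None of this defends the trigger. Nor is it a detail left to an unseen analysis plan, since the article states the rule outright.

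**Conclusion.** The concern holds for the supportive adjusted model, at moderate severity. The per-covariate probability of about one half rests only on randomization and the planned arm size, and calling an SMD above 0.10 a substantial imbalance is not justified at 100 per arm. That about 5 of the 10 items would enter is an expectation; it treats each listed item as one varying covariate, which is rough for comorbidities and preoperative medications. The loss of a little under 4 points of power depends on assumed effects and shows only the order of size. It would be smaller if the collected factors predict PONV weakly in this population.

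**What to change.** Keep SMDs as a description of balance, and remove both the model trigger and the label attached to 0.10. Before unblinding, name a short list of prognostic covariates that enter the logistic model whatever their observed balance: for example, age plus Apfel score, or in place of the score the individual risk factors that vary at baseline, such as smoking status and prior PONV. Using the score and its overlapping factors together adds little. Female sex is constant here, and actual postoperative opioid use arises after randomization, so neither belongs on the list.

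Optionally, also report a marginal RR standardized from this model, with 95% CI, so that the adjusted and unadjusted effects are on one scale.

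The cost is wording only. The covariates are already on the case report form, and the article describes recruitment as ongoing, so the list can be fixed without sight of grouped data.

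### At the trial's own planning rates, a difference in median NRS scores will be 0 in nearly every trial, even when taVNS works as planned

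*Protocol article*

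**What the plan says.** In the Protocol article, the Statistical plan compares NRS scores between groups by the independent t-test or the Mann-Whitney U test, "with the effect size reported as the difference in means or medians with 95% CI". It names no other effect measure for the NRS. Earlier in the same section, continuous variables are summarised by means if normally distributed and otherwise by medians, and the Kolmogorov-Smirnov "test will be used to detect the normality of distribution". All secondary endpoints are analysed in the ITT population, so patients without symptoms are included.

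The Outcome section takes the NRS at 1, 2, 6, 12 and 24 h and anchors 0 at no nausea. It also states that "PONV is defined as the occurrence of any episode of nausea" and/or vomiting over the 24 h.

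The Sample size section says that the sham-type incidence "is approximately 40% following dual-agent prophylaxis with dexamethasone and ondansetron", and for the other arm "we assume that the incidence of PONV in the taVNS group would be reduced to 20" per cent. It continues: "To provide a significance level of 0.05 and a power of 0.8, a sample size of 158 patients will be required", and "the recruitment target will be increased to 100 patients in each group".

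**The concern.** A patient without PONV over 24 h has had no nausea and scores 0 at all five time points. If fewer than half of the patients in each arm have any PONV, the median score is 0 in both arms and so is their difference. The plan's own rates put both arms below half.

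NRS severity is one of three secondary comparisons tested at 0.017, and the Discussion gives clinical weight to a reduction in nausea severity. If the measure is followed as written, a treatment that halves PONV would most likely be reported with a significant p-value and a median difference of 0. A reader could take that for no difference in severity, or could not reconcile it with the test.

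**Working it through.** **Inputs from the article.** PONV over 24 h: 40% sham, 20% taVNS (Sample size). 100 per arm (Sample size), 1:1 (Randomization and blinding). NRS 0 = no nausea (Outcome). ITT, t-test or Mann-Whitney, secondary alpha 0.05/3 (Statistical plan).

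**The plan's own figure first.** Two proportions, unpooled variance, two-sided 0.05, power 0.80:
n = (1.960 + 0.842)² × (0.4×0.6 + 0.2×0.8) / 0.2² = 78.49, so 79 per arm and 158 in total. This reproduces the stated 158 and confirms that 40% and 20% are the working rates.

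**Step 1: share of zeros.** At least 1 − 0.40 = 60% of sham and 1 − 0.20 = 80% of taVNS patients score 0 at every time point. Both population medians are 0 at each time point, and also for a worst or summed 24 h score. No assumption about severity among affected patients is needed.

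**Step 2: which branch is taken.** A jump of at least 0.6 in the distribution at 0 leaves a gap of at least 0.3 from any continuous curve. In simulated trials the Kolmogorov-Smirnov test rejected normality in 100%.

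**Step 3: chance that a sample median exceeds 0.** With 100 per arm this needs at least 50 patients scoring above 0:

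| Arm and share above 0 | P(sample median > 0) |
|---|---|
| Sham, 40% (worst 24 h score) | 0.027 |
| taVNS, 20% (worst 24 h score) | about 2×10⁻¹¹ |
| Single time point, 30% (assumption) | 0.00002 |

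So both medians are 0 with probability about 1 − 0.027 = 0.97 for a worst score.

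**Step 4: simulation.** 100 per arm; severity uniform on 1–10 among affected patients (assumption); percentile bootstrap intervals. The single-time-point rates are also assumptions, because the article gives none.

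| Score | Median difference exactly 0 | CI exactly 0 to 0 | Mean difference (taVNS − sham) |
|---|---|---|---|
| Worst 24 h, 40% vs 20% | 97% | 46–48% | −1.1 |
| Single time point, 30% vs 15% | 100% | 98% | −0.8 |
| Single time point, 20% vs 10% | 100% | 100% | −0.5 |

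The mean difference agrees with direct arithmetic: (0.20 − 0.40) × 5.5 = −1.1. With milder or more moderate severity distributions the worst-score mean difference ran from about −0.65 to −1.19, and the median difference was still 0 in 96–97% of trials.

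**Step 5: the test beside the estimate.** For the worst score, Mann-Whitney was significant at 0.0167 in 76% of trials, and 73% of all trials paired a significant result with a zero estimate. That is 73/76 = 96% of the significant ones. With PONV almost abolished by taVNS (40% vs about 0%), the median difference was still 0 in 97.6% of runs.

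**Step 6: alternatives.** A Hodges-Lehmann shift was 0 in at least 99.7% of runs at 40% vs 20%, so it does not help. The probability index does. If severity among affected patients is the same in both arms:
- taVNS 0, sham above 0: 0.80 × 0.40 = 0.32
- both 0 (tie): 0.80 × 0.60 = 0.48
- both above 0: 0.20 × 0.40 = 0.08, which counts half by symmetry

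Index = 0.32 + 0.48/2 + 0.08/2 = 0.60, against 0.50 for no effect.

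**The case against.** **The link to the normality test is not explicit.** The normality sentence concerns how variables are summarised, and the NRS sentence stands apart from it. A reader might infer that the plan expressly lets the Kolmogorov-Smirnov test choose the NRS effect measure. It does not say so. It is the only selection rule given, though, so it is the natural reading. The text would also allow a mean difference, but nothing in it secures one.

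**The confidence interval.** A reader might infer that the interval collapses to 0 to 0 in every case. That holds at the assumed single-time-point rates. For a worst 24 h score it was exactly 0 to 0 in only about half of trials; in one set of runs the upper limit had a median of 0.5 and a 90th percentile of 2.

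**Dependence on 40%.** A reader might infer a zero estimate at any event rate. The Introduction gives 30%–40% for moderate to severe PONV, citing among others the source used for the 40%, while the endpoint counts any episode. If sham incidence is higher, a worst-score median can exceed 0: the probability is 0.54 at 50% and 0.98 at 60%. At 50% vs 25% the median difference was 0 in only 45–47% of simulated trials. This limit stands.

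**Other information remains.** Mann-Whitney is valid, the primary relative risk estimates the incidence component, and interquartile ranges would show the direction for a worst score, though usually not at 20% vs 10%. This is correct, but none of these is the effect size with interval that the plan promises for severity.

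**Data-driven choice of method.** A reader might also infer error inflation from the normality gate. None is shown: when the check is practically certain to fail, the method is in effect fixed beforehand.

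**Left to the statistical analysis plan?** The article names the measure, so this is a stated choice that works badly, not a missing detail.

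**Conclusion.** The point holds at the trial's planning rates. If the median branch is followed, the NRS estimate will be 0 practically always at the single time points, and in about 97% of trials for a worst 24 h score with 100 per arm, usually beside a significant Mann-Whitney result. The zero medians rest only on the 40% and 20% rates, the zero anchor and the ITT set. The mean differences, the Mann-Whitney rates and the interval results also rest on the assumed severity distribution, and the single-time-point results on assumed rates.

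The defect lies in the effect measure for one secondary endpoint. The documents do not support a claim that the test is invalid, that the interval is always 0 to 0, or that the estimate is 0 whatever the sham rate.

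**What to change.** In the secondary-endpoint paragraph of the Statistical plan:

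- Pre-specify the Mann-Whitney test for the NRS, with no normality check.
- Replace the median difference by the probability that a taVNS patient scores lower than a sham patient, ties counted as half, with 95% CI.
- Add the mean difference with a bootstrap 95% CI, to give the effect in NRS points.
- Do not substitute a Hodges-Lehmann shift.

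These measures remain usable if sham incidence turns out above 50%. The cost is wording only: no change to design, sample size, data collection, test or alpha. Recruitment is under way, and the article says that statistical plans will be final before unblinding, so the change can still be made blind. The primary endpoint is unaffected.
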